### I-MUR

This will take place in the pharmacy private consultation area. The estimated time for the consultation will be 26 minutes based on phase one experience.

### Data collection

Data collected during the I-MUR will include patient demographics, their regular medications (active ingredients) including those used for asthma, patients’ attitude towards their medications and adherence to treatments assessed during the I-MUR interview, PCIs identified by the pharmacist, pharmacist’s advice given to patients, including healthy living advice, pharmacist’s advice given to doctors, pharmacist’s own view on the potential benefit to the patient of the MUR service they provided.

Following each consultation, pharmacists will be required to enter the data from each consultation into the web-based template provided, maintaining patient anonymity. This process was developed and tested during earlier work [21].

Data collected at multiple time points will be patients’ responses to ACT, adherence to asthma treatment and number of active ingredients (see Figure 2).

**Figure 2 Fig2:**
[figure not shown]
Study timeline, showing activities provided by pharmacists and information gathered.

### Proposed sample size

It is aimed to obtain a final sample size of 360 pharmacists and 1800 patients, requiring each pharmacist to provide the intervention to five patients. The power calculation for this study has been conducted taking into consideration the intra-cluster and inter-cluster correlation (ICC) using SPSS sample power calculation. The ICC represents the correlation between responses of individuals in the same clusters which is a proportion of the total variation explained by variation between clusters [28] and its value ranges between 0 and 1. For this study it was decided to use an ICC = 0.02 as this was used in a similar study conducted in Australia [17]. This is based on an estimated 20% difference in asthma severity (ACT score), which may be achieved, again based on the Australian study [17], which found that the proportion of patients classified as having severe asthma declined from 87.9% to 52.7% following pharmacist intervention. This is based on an anticipated 40% improvement in asthma severity following pharmacist intervention; the difference will be measured by comparing the ACT score gathered at baseline to T3, T6, T9 for each patient, where an ACT score ≤ 19 means not well controlled asthma and an ACT score ≥ 20 well controlled asthma.

Four options were considered (Table 1) all using d = 20% and alpha = 0.05, but considering different numbers of pharmacists and patients per pharmacy. Option d was chosen, as it has a power of 95%. The calculated ratio between pharmacists and patient in order to achieve the above results is 1:4. The attrition rate was estimated as 23% based on the Australian study, which had an attrition rate of 14%, but following which the authors suggested that this percentage could be in the range of 14-25% [17]. Therefore pharmacists will be required to recruit five patients instead of four. Based on an attrition rate of 23%, 396 patients will not complete the study, leaving 1386, which is still sufficient to attain option d (693 patients per group).

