An Australian multi-site randomised controlled trial compared pharmacist counseling on asthma, asthma medication and associated lifestyle advice with a control group providing usual care. Fifty pharmacies were enrolled and randomly allocated to one of the two groups (randomisation conducted at pharmacy level), the intervention group with 191 patients and the control group with 205 patients. In both groups questionnaires and spirometric testing were carried out at baseline and at six months. The main outcome measure was asthma severity/control status assessed by a tool adapted from the National Asthma Council. The percentage of patients in the intervention group classified as having severe asthma declined from 87.9% to 52.7% (p < 0.01), whilst the change in the control group the change was not significant (71.2% to 67.9%; p = 0.11). These authors used a multilevel logistic regression model to adjust for the difference in asthma severity at baseline and to account for any possible effect from clustering. Both pharmacist groups administered questionnaires and spirometric testing at baseline and six months later; it was found that patients in the intervention group were almost three times more likely to change from the severe asthma category to the not severe category than patients in the control group (OR 2.68, 95% CI 1.64 to 4.37 p < 0.01) [17].

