### Medicines use reviews in asthma

The Medicines Use Review (MUR) service was first introduced in England in 2005 as an advanced service in the community pharmacy contractual framework. The aim of the MUR is to achieve a concordant consultation about medicine-taking by establishing the patient’s actual use, understanding and experience of taking their medicines, with the ultimate aim of improving the clinical and cost-effectiveness of prescribed medicines, reducing medicines wastage and improving patient outcomes through improved adherence [18].

Portlock et al. [19] conducted a study in England in which 965 MURs were undertaken in patients with asthma. Pharmacists identified that 37% of the patient population were primarily non-adherent (i.e. collected < 75% of intended asthma prescriptions in the previous 12 months) and a further 31% had secondary adherence issues (i.e. not taking their medications in the way they had been intended). Pharmacists made 1,787 interventions (mean 1.8 per MUR consultation) of which 41% were device checks, 10% were referral to a GP or nurse and 49% were educational.

Another study involving 154 patients with asthma receiving an MUR found that the proportion of patients whose asthma was not controlled fell from 59% to 45% (p < 0.01), 30% of patients were referred to their GPs or asthma nurse as a result of their MUR and, of those referred, 70% had a treatment or dosage change [20].

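### The 95% power at 693 patients per group belongs to a small effect (most plausibly 0.20 SD in ACT score), not to the 20% difference or 40% improvement given as its basis

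*Protocol article*

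**What the plan says.** All of this stands in the Proposed sample size section of the protocol article and its Table 1.

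- The effect is described first as "This is based on an estimated 20% difference in asthma severity (ACT score), which may be achieved". It is tied to an Australian trial in which "the proportion of patients classified as having severe asthma declined from 87.9% to 52.7% following pharmacist intervention".
- Two sentences later the basis is different: "This is based on an anticipated 40% improvement in asthma severity following pharmacist intervention". That sentence goes on to say that ACT scores will be compared with baseline at T3, T6 and T9, and it gives the 19/20 cut-off for control.
- The calculation itself is summarised as "Four options were considered (Table 1) all using d = 20% and alpha = 0.05". Table 1 repeats d = 20% and ICC 0.02 for each option. It shows no SD, mean or control proportion.
- The choice is justified by "Option d was chosen, as it has a power of 95" per cent. Option D has 173 pharmacists and 693 patients per group, at four patients per pharmacist.
- On losses: "Based on an attrition rate of 23%, 396 patients will not complete the study, leaving 1386".

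The Background section on the pharmacists' role also prints the control arm of the Australian trial: "71.2% to 67.9%; p = 0.11". The section on medicines use reviews in asthma cites an English study in which "the proportion of patients whose asthma was not controlled fell from 59% to 45" per cent.

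**The concern.** A power statement means something only for a stated effect on a stated endpoint. Here one calculation has two verbal bases, 20% and 40%, and the symbol d carries a percent sign with nothing to show what it is a percentage of. The paragraph also moves between the ACT score and the proportion on either side of the cut-off.

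The 40% is the relative fall within the intervention arm of the cited trial. It takes no account of the control arm, although the present trial compares randomised groups.

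What is at stake is interpretation. The trial is meant to inform national policy. If 693 per group was sized for a much smaller effect than the text names, a significant result could be read as confirming a 20% or 40% target that the calculation never addressed.

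**Working it through.** **Inputs from the document.** Alpha 0.05 (sidedness not stated), ICC 0.02, cluster size m = 4 or 5, and the n per group in Table 1. Rates: 87.9% to 52.7% and 71.2% to 67.9% (Australian trial), 59% to 45% (English study).

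**Step 1. Reproduce Table 1 with d = 0.20 SD.** Design effect DE = 1 + (m − 1) × 0.02, which is 1.08 for m = 5 and 1.06 for m = 4. Unclustered n = 2(z₁ + z₂)²/d², with z₁ = 1.96 and z₂ = 1.282 (90%) or 1.645 (95%). This gives 526 and 650 per group. Power = Φ(0.20 × √(n/(2·DE)) − 1.96).

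| Option | n needed | n in Table 1 | Power at Table 1 n | Power stated |
|---|---|---|---|---|
| A | 526 × 1.08 = 568 | 575 | 90.4% | 90% |
| B | 526 × 1.06 = 558 | 560 | 90.2% | 90% |
| C | 650 × 1.08 = 702 | 700 | 95.0% | 95% |
| D | 650 × 1.06 = 689 | 693 | 95.1% | 95% |

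For option D, a one-sided alpha would give 97.6% and ignoring the ICC 96.1%. The two-sided calculation with the ICC is therefore the one that matches.

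**Step 2. Is that the only reading that fits?** No. For two proportions, n = [z₁√(2p̄(1 − p̄)) + z₂√(p₁(1 − p₁) + p₂(1 − p₂))]²/(p₁ − p₂)², where p̄ is the mean of the two. For 50% versus 40% at 95% power this is 641, and 641 × 1.06 = 679 for option D; power at 693 is 95.4%. The other three rows fit about as well. This is a 20% relative reduction, or 10 points. No 50% control rate is printed.

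**Step 3. Size the effects that the text names.** Same formula, 95% power, DE 1.06, nearest whole patient.

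| Effect | n per group | Power at 693 |
|---|---|---|
| 20 points, from 59%, 67.9%, 71.2%, 87.9% | 170, 165, 161, 116 | above 99.99% in each case |
| 60% versus 40% (worst case for 20 points) | 170 | above 99.99% |
| 20% relative, from 59%, 67.9%, 71.2%, 87.9% | 490, 352, 311, 144 | 99.0% to above 99.99% |
| 87.9% versus 52.7% (the 40%) | 43 | about 100% |
| 67.9% versus 52.7% (Australian arms at follow-up) | 283 | about 99.99% |

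A 20% difference in mean ACT needs at most about 111 per group, assuming a mean of 15 to 19 and an SD of 3 to 6. Neither assumption comes from the document.

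**Step 4. Where the 40% comes from.** (87.9 − 52.7)/87.9 = 35.2/87.9 = 40.0%, within one arm. The control arm fell by 71.2 − 67.9 = 3.3 points. The between-arm figures are therefore 67.9 − 52.7 = 15.2 points at follow-up, or 35.2 − 3.3 = 31.9 points as a difference in changes.

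**Step 5. What 693 per group can detect.** On the score: 0.20 SD, which is 0.6 to 1.2 ACT points if the SD is 3 to 6 (assumed). On the proportion: about 9.9 points near 50% to 60%.

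These are not the same effect. If the score is roughly normal, a 0.20 SD shift moves at most Φ(0.1) − Φ(−0.1) = 8.0 points across a cut-off. Binary power for 8.0 points at 693/1.06 is about 82%.

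**Step 6. Attrition.** 0.23 × 1800 = 414, and 0.77 × 1800 = 1386 = 2 × 693. The printed 396 is 22% of 1800, and 1800 − 396 = 1404.

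**The case against.** The strongest defence is that the numbers are right. Table 1 reproduces to within rounding, d is the usual symbol for a standardised difference, and the primary outcome is the ACT score, analysed as a continuous variable by repeated measures ANOVA under Data analysis. On that view the percent sign is a slip of notation, the cut-off only helps to interpret the score, and no patient number changes. Most of this stands, and it limits the point to what the power is said to be for.

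Four stronger readings are tempting and are not supported:

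- That the sample size is wrong or the trial underpowered. For a 20-point difference, for a 20% relative reduction from the printed baseline or control-arm rates, and for 87.9% versus 52.7%, power at 693 is above 95%. A relative reduction does depend on its base: 20% off a 30% rate would need about 1,500 per group, with 68.6% power at 693. No such rate is in the document.
- That d must be an SD unit. The 50% versus 40% reading also fits, and the document prints neither 0.20 SD nor a 50% control rate.
- That 0.20 SD and 10 percentage points are interchangeable. Step 5 of the working shows that they are not.
- That the evaluable number is wrong because 1800 − 396 = 1404. The 1386 is exactly 77% of 1800; only the 396 is a slip.

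The defence does not remove the contradiction between the two bases. Nor is this detail that can be left to an analysis plan: the article states the basis, and states it inconsistently.

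**Conclusion.** The point holds as a misattributed effect. Table 1's 693 per group and 95% power match a small effect: most plausibly 0.20 SD in ACT score, possibly 50% versus 40% in the proportion not controlled. They do not match the effects named in the text. 693 is about 4 times what a 20-point difference needs (693/170), about 1.4 to 4.8 times what a 20% relative reduction from the printed baseline or control-arm rates needs (693/490 to 693/144), and about 16 times what 87.9% versus 52.7% needs (693/43). The 20% and 40% statements also contradict each other, and the 40% is not a between-group effect.

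The conclusion rests on two-sided alpha, normal-approximation formulas, the ICC of 0.02 and the printed rates. Which of the two fitting scales was used cannot be settled from the document. The conversion to ACT points depends on an assumed SD. The attrition slip is 414 − 396 = 18 patients and does not affect the power.

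**What to change.** 1. Confirm the scale of d from the output of the sample-size software, and name the powered endpoint: mean ACT score, or the proportion with ACT of 19 or less.
2. If d is standardised, state: with 693 analysed patients per group, ICC 0.02 and two-sided alpha 0.05, the trial has 95% power for a between-group difference of 0.20 SD in ACT score. Add the assumed SD and the resulting difference in ACT points.
3. If d is binary, state the control rate and the detectable difference (about 10 points near 50%).
4. Give one of these statements, and do not present 0.20 SD and 10 points as equivalent.
5. Remove the 20% difference and the 40% improvement as the basis for the power.
6. In the attrition sentence change 396 to 414, and keep 1386 and 693 per group.

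The cost is wording plus a look at the software output. Enrolment, pharmacist numbers and analysis stay as they are. The stated target effect will look more modest.

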**Table 1 Tab1:** **Elements for the evaluation of the power analysis**

**Options**	**Power level**	**ICC**	**d**	**Alpha**	**Number of pharmacists per group**	**Number of patients per group**	**Pharmacists patients ratio**
A	90%	0.02	20%	0.05	115	575	1:5
B	90%	0.02	20%	0.05	140	560	1:4
C	95%	0.02	20%	0.05	140	700	1:5
D	95%	0.02	20%	0.05	173	693	1:4

### Data analysis

In studies where the important baseline factors seem well balanced, it is likely that any differences in outcome between intervention and control groups are a real effect of treatment, which is one component of the internal validity. Patients’ location, age, gender and ACT score will be collected and compared at baseline. This baseline ACT score will provide information regarding the level/severity of asthma prior to intervention delivery.

Quantitative data gathered through the web platform (Qualtrics^©^) will be exported and analysed using SPSS version 22. Patient location, age, gender and ACT score will be compared at baseline.

Asthma severity assessed by ACT score will be analysed over time within individual patients to obtain a percentage change score. Scores will be compared between groups at all times points. The number of active ingredients in use and reported adherence to treatment will be compared at three time points after provision of the I-MUR. The number of PCIs identified and advice given by pharmacists will be captured for both groups separately and combined. Any change in the severity of asthma and the accompanying percentage variation in cost (based on peer reviewed published data) will also be assessed. It will be possible to compare data before and after the I-MUR intervention for group A and B, separately and combined. In addition findings will be analysed by region.

A significance level (alpha) of 0.05 will be used in all analyses. Between-group differences at baseline will be compared using independent Student’s t-test for continuous parameters and Pearson’s χ^2^ will be used for categorical parameters. Outcomes for continuous parameters will be evaluated using repeated measures multivariate ANOVA.

The analysis will be conducted in two steps. Step one will represent an interim analysis after the first six months, after completion of T6, by which time all patients will have been followed up for three months after the intervention. Step two will represent the final analysis, which will be conducted at the end of the study after T9.

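### Apparent baseline balance is taken to make any outcome difference likely real, and the only balance checks are significance tests that would miss a true 0.10 SD shift in ACT about 44% of the time

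*Protocol article*

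**What the plan says.** The Data analysis section of the protocol article opens with a general premise. Of studies whose main baseline factors look alike, it says "it is likely that any differences in outcome between intervention and control groups are a real effect of treatment". It calls this one component of internal validity. It then names the factors: "Patient location, age, gender and ACT score will be compared at baseline". The method follows: "Between-group differences at baseline will be compared using independent Student’s t-test for continuous parameters", while Pearson's chi-square "will be used for categorical parameters". On the threshold it says "A significance level (alpha) of 0.05 will be used in all analyses". No other criterion of balance is given.

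For ACT itself the section names three things: a percentage change score within patients, a comparison of scores between groups at all time points, and repeated measures multivariate ANOVA for continuous outcomes. The Proposed sample size section also describes comparing each patient's baseline ACT with T3, T6 and T9. No adjustment of the between-group comparison for T0 ACT is named.

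**The concern.** The premise is wrong in two ways.

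- Balance on four measured factors does not make an outcome difference real. Chance remains, and so does bias from a patient-completed outcome in a trial where neither pharmacists nor patients can be blinded.
- A non-significant t-test or chi-square test does not show that the groups are balanced. It shows only that the data did not rule out equality.

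Systematic imbalance is plausible here. Pharmacists choose about five patients each from their own records, referrals and prescriptions. They cannot be blinded, and only group A receives I-MUR training before T0, so a pharmacist may know the arm when selecting patients. The check on location adds little, because randomisation is stratified by region.

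At stake is how the T3 comparison is read, the only follow-up visit at which group B has not yet had the I-MUR. A difference in who was recruited could pass as balanced, and the premise would then support calling the resulting ACT difference a treatment effect.

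**Working it through.** **Inputs.** From Proposed sample size and Table 1: ICC 0.02, d = 20%, alpha 0.05, option D with 693 patients per group at 4 per pharmacist, and 1800 recruited at 5 per pharmacist (900 per group). Assumed: two-sided tests, a true baseline ACT shift of 0.10 SD, a T0–T3 correlation ρ of 0.5 to 0.7, and no I-MUR effect.

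**Step 1: reproduce Table 1.** Design effect DE = 1 + (m − 1) × 0.02. Power ≈ Φ(0.20/SE − 1.96), with SE = √(2·DE/n) in SD units.

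| Option | DE | n per group | Power found | Power stated |
|---|---|---|---|---|
| A | 1.08 | 575 | 90.4% | 90% |
| B | 1.06 | 560 | 90.2% | 90% |
| C | 1.08 | 700 | 95.0% | 95% |
| D | 1.06 | 693 | 95.1% | 95% |

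So d behaves as 0.20 SD. A 20-percentage-point difference in proportions would need only about 116–170 per group for 95% power, which does not fit the table. Half the target effect is therefore 0.10 SD.

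**Step 2: miss rate of the baseline ACT t-test.** The planned test ignores clustering, so its cut-off uses √(2/900) = 0.0471, giving 1.96 × 0.0471 = 0.0924 SD. The true sampling SE is 0.0471 × √1.08 = 0.0490. For a true shift of 0.10 SD:

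P(miss) ≈ Φ((0.0924 − 0.10)/0.0490) = Φ(−0.155) = 44%.

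The same formula gives 80% at 0.05 SD, 12% at 0.15 SD and 1% at 0.20 SD. With a cluster-adjusted test the figure at 0.10 SD is 47%. At 693 per group it is 54%, but those are the completers; the baseline test has the recruited patients.

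**Step 3: what the shift does at T3** (900 per group, cluster-correct outcome tests, SE = 0.0490). Either the 0.10 SD shift persists in full, or it fades to 0.10ρ. In each case error ≈ Φ(|bias|/SE − 1.96) + Φ(−|bias|/SE − 1.96).

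- Raw T3 difference: bias 0.10 or 0.10ρ; SE 0.0490.
- Change from T0: bias 0 or 0.10(1 − ρ) in size; SE 0.0490 × √(2(1 − ρ)).
- Adjusted for T0: bias 0.10(1 − ρ) or 0; SE 0.0490 × √(1 − ρ²).

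Example, change score, fading shift, ρ = 0.5: 0.05/0.0490 = 1.02, so Φ(−0.94) + Φ(−2.98) = 17.5%.

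| ACT comparison at T3 | Shift persists, all trials | Shift persists, baseline test passed | Shift fades, all trials | Shift fades, baseline test passed |
|---|---|---|---|---|
| Raw difference | 53% | 25–35% | 18–30% | about 7% |
| Change from T0 | 5% | about 5% | 12–18% | 6–7% |
| Adjusted for T0 ACT | 14–22% | 14–22% | 5% | 5% |

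Ranges run over ρ = 0.5 to 0.7. The columns for trials that passed the baseline test come from simulated bivariate-normal group differences. Under a persisting shift, percentage change on a rounded 5–25 scale (assumed means 16–19, SD 4–5) gave 4.7–5.9%, so it behaves like absolute change there.

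**Step 4: precision.** The variance of the adjusted estimate relative to the change score is (1 − ρ²)/(2(1 − ρ)) = (1 + ρ)/2, which is 0.75 at ρ = 0.5 and 0.85 at ρ = 0.7. Adjustment therefore lowers variance by 25% to 15%.

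**The case against.** The strongest reply is that the planned ACT analyses already use T0. Percentage change does, and with T0 among the repeated measures the group-by-time term of the ANOVA compares changes. If a recruitment difference persists in full, a change score stays near 5%, while adjustment for T0 leaves 14–22%. This stands. A reader might infer from the table that 25–35% of null trials passing the baseline check would be declared positive. The documents do not support that as the size of the problem: it needs a raw T3 comparison and a fully persisting shift. The line about comparing scores between groups at all time points could mean raw or change scores.

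A reader might also infer a rule that p > 0.05 means balanced and so the effect is real. The text does not say that. Its premise speaks of studies in general and is hedged, and no analysis is made to depend on the baseline tests. The link from premise to tests is an inference, although the tests are the only balance checks the section offers.

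Nor does the article give an imbalance of 0.10 SD. It is an assumed systematic shift. With 900 per group, an observed gap of 0.10 SD would be flagged, since the cut-off is 0.092 SD.

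Finally, baseline tests are a common habit, and an article may leave a covariate list to the analysis plan. That is fair for the covariates. It does not cover the premise, which is stated and wrong.

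**Conclusion.** The point holds in a limited form. The inference from apparent balance to a real effect is unsound, and the tests at 0.05 are weak evidence of balance: about 44% of true 0.10 SD shifts in ACT would go unflagged with the 900 per group recruited. This rests on d being 0.20 SD, ICC 0.02, two-sided testing and an assumed shift.

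The consequence is not one number. It depends on which ACT comparison is read and on how the shift behaves after T0. No single analysis is safe in both scenarios: change from baseline is safe if the shift persists, and adjustment for T0 is safe if it fades or is due to chance. A baseline p-value cannot tell these apart, which is why it should not support the conclusion. Because the planned change and repeated measures analyses already use T0, severity is minor to moderate.

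**What to change.** 1. Delete the sentence that infers a real effect from apparent balance.
2. Report location, age, gender and ACT by group descriptively, and do not use t-tests or chi-square tests as evidence of comparability.
3. State that the between-group ACT comparison at each visit comes from a model that allows for pharmacist clustering and always includes T0 ACT and region (the stratification factor), whatever the baseline comparison shows. Age and gender are optional.
4. Show change from baseline as a sensitivity analysis, and say plainly that no adjustment removes a recruitment bias that persists in full.

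The cost is a few sentences and one sensitivity analysis. T0 ACT and location are already collected. The gain is 5% error under chance imbalance or a fading shift, with 15–25% less variance than a change score at correlations of 0.7 to 0.5. What is given up is the use of baseline p-values as support for comparability.

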### ACT

The ACT (primary outcome measure) is a patient-completed questionnaire with five items assessing asthma symptoms (daytime and nocturnal), use of rescue medications, and the effect of asthma on daily functioning. Each item includes response options corresponding to a 5-point Likert scale, which are summed to yield a score ranging from 5 (poor asthma control) to 25 (complete asthma control). Schatz et al. [27] found that a cut off score of 19 or less identifies patients with poorly controlled asthma.

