### Primary outcome measure

#### Primary outcome

Severity of asthma: before, during and after the I-MUR service provision assessed using the ACT score.

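### Percentage change does not suit ACT: before/after means drift upward when nothing changes, and the between-group comparison loses precision

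*Protocol article*

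**What the plan says.** All places are in the protocol article.

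- **Primary outcome:** asthma severity, "assessed using the ACT score". No percentage is mentioned there.
- **ACT:** five items "which are summed to yield a score ranging from 5 (poor asthma control) to 25 (complete asthma control"), with 19 or less marking poor control.
- **Data analysis:** "Asthma severity assessed by ACT score will be analysed over time within individual patients to obtain a percentage change score". The next sentence reads "Scores will be compared between groups at all times points", without saying whether these are raw or percentage scores.
- **Data analysis, before/after:** "It will be possible to compare data before and after the I-MUR intervention for group A and B, separately and combined".
- **Data analysis, model:** "Outcomes for continuous parameters will be evaluated using repeated measures multivariate ANOVA".
- **Data analysis, baseline:** "Patient location, age, gender and ACT score will be compared at baseline".
- **Proposed sample size:** each patient's baseline ACT is to be compared with T3, T6 and T9, using the 19/20 cut-off. Table 1 uses d = 20%, ICC 0.02 and alpha 0.05. Option D has 95% power with 173 pharmacists and 693 patients per group.

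**The concern.** A percentage change has a fixed meaning only on a scale with a true zero. The lowest possible ACT score is 5, so the ratio of two scores is arbitrary. A 2-point gain is +20% from a baseline of 10 and +10% from a baseline of 20. Crossing the plan's own control threshold, 19 to 20, is only +5.3% (1/19).

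The measure is also asymmetric. Gains from a low baseline are divided by a small number and equal losses from a high baseline by a large one, so ordinary visit-to-visit variation yields a positive average. A before/after mean on this scale can suggest that I-MUR helped when mean ACT has not moved. In the comparison between groups, dividing by a noisy baseline adds variance and so costs power.

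The document fixes this score for the primary measure; it is not a detail left open for an analysis plan to settle.

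**Working it through.** **1. Reproduce the plan's sample size.** Inputs from Proposed sample size and Table 1: alpha 0.05 (taken as two-sided), power 95%, ICC 0.02, 4 patients per pharmacist, d = 20% read as a standardised difference of 0.20.

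- n per group = 2 × (1.960 + 1.645)² / 0.20² = 650 (rounded up).
- Design effect = 1 + (4 − 1) × 0.02 = 1.06.
- 650 × 1.06 = 689, which needs 173 pharmacists, or 692 patients. Table 1 states 173 and 693.
- Options A, B and C come out at 570, 560 and 705, against 575, 560 and 700 stated.

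Read instead as a 20-point difference in proportions (0.60 against 0.40), option D would need about 160 × 1.06 = 170 per group. So Table 1 fits a standardised mean difference. The article does not say so; this is inferred from the fit.

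**2. The drift, by arithmetic.** One patient goes from 15 to 20 (+33.3%) and another from 20 to 15 (−25.0%). Mean change in points is 0. Mean percentage change is (33.3 − 25.0)/2 = +4.2%.

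For equal means and SDs at both visits, the drift is to second order (1 − correlation) × (SD/mean)². With mean 18, SD 4 and correlation 0.6 this is 0.4 × (4/18)² = 2.0%.

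**3. The drift, by simulation.** The article gives no ACT mean, SD or visit correlation, so these are assumed: means 16, 18, 20; SDs 3, 4, 5; correlations 0.4, 0.6, 0.8 (27 combinations). Scores are bivariate normal, rounded and held to 5-25, with 1,000,000 patients per combination and no true change.

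- Mean change in points: 0.0 throughout, to within 0.01.
- Mean percentage change: +2.4% in the middle case (18, 4, 0.6), range +0.5% to +7.7%.
- Test in one group, with 693/1.06 = 654 effective patients: in the middle case the SD of percentage change is 22.5, so z = 2.36/(22.5/√654) = 2.7. The range is 1.3 to 4.5, and z is at least 2.0 in 21 of the 27 combinations.
- Both groups pooled (1386 patients): a nominal 5% test rejects in 41-100% of trials.

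**4. Precision between groups.** True effect 0.20 SD, power = Φ(e√(654/2) − 1.96), where e is the standardised effect of each measure. Middle case:

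| Measure | e | Power |
|---|---|---|
| Percentage change | 0.198 | 95% |
| Change in points | 0.219 | 98% |
| ACT in points, adjusted for T0 | 0.246 | 99% |

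Efficiency of percentage change against change in points is (0.198/0.219)² = 0.82. Change in points against baseline adjustment is (0.219/0.246)² = 0.79. The product is 0.65, so percentage change needs 1.54 times the patients of the adjusted analysis. Over the 27 combinations this ratio runs from 1.20 to 2.15. Power is 73% to over 99% with percentage change and 96% to over 99% with adjusted ACT.

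On a narrower set (mean/SD of 18/4.5, 17/5 and 19/4, each with correlations 0.5, 0.6 and 0.7), power is about 84-99% with percentage change, 94-99% with change in points and 98-100% with adjusted ACT.

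**The case against.** **The randomised comparison is not biased by the drift.** A reader might infer that percentage change would make I-MUR look effective against the control group. That does not follow. With randomised groups and similar baselines the drift is about equal in both and cancels in expectation. This stands in full: spurious improvement is confined to within-group and pooled before/after means, which the article introduces permissively.

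**Percentage change may not be the main analysis.** The primary outcome is the ACT score, and both the between-group comparison of scores and the repeated measures ANOVA may refer to raw ACT. This also stands as a possible reading. It leaves the percentage score in place without saying which variable carries the inference.

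**Baseline ACT is not confined to balance checks.** Proposed sample size compares it with T3, T6 and T9, and it would naturally be one of the repeated measures. It is only not named as a covariate, and an article may leave covariates to the full plan. Their absence is no fault in itself.

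**Not all the lost efficiency comes from the percentage scale.** This stands: about half of it is the difference between a change score and baseline adjustment.

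**The power loss is modest.** In the middle case percentage change still gives 95%, the planned figure. The documents do not support a claim that the trial is underpowered on this account.

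**Conclusion.** The point holds in a limited form. The article fixes a percentage change score for a scale with no zero. That fits neither the stated primary outcome nor the standardised difference of 0.20 that Table 1 appears to use.

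Its firm consequence is for before/after means, which are pushed upward with no true change by about +0.5% to +8%, enough to reach nominal significance under most of the assumed values. Its consequence for the randomised comparison is lost precision. That loss ranges from negligible to material: 73% power in the worst combination examined (mean 20, SD 5, correlation 0.4) against 96% with adjustment.

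The sizes depend on assumed ACT means, SDs and correlations, on normal scores before rounding, and on the ICC of 0.02 applying to every measure. The directions did not change in any combination. The change is worth making because it costs nothing, not because the trial would otherwise fail.

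**What to change.** In Data analysis:

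- Replace the percentage change score by ACT in points.
- Base the primary inference on the between-group difference in ACT points while group B is still untreated (the T3 score, taken before its I-MUR), adjusted for T0 ACT and allowing for clustering by pharmacist.
- Report the proportion with ACT of 20 or more as supporting information, using the cut-off already in the article.
- State that within-group or pooled mean percentage change will not be interpreted as an effect of I-MUR.

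Baseline ACT is already collected, so the cost is analysis wording only: no new data, visits or patients.
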